#### Control

The control group will be placed on a waitlist for the Parent Web which they will be able to participate in following post-intervention data collection (i.e., after 6 to 8-weeks). No additional services will be provided to the control group during the wait-list period.

### Data collection and management plan

The Parent Web is accessed through an encrypted web-portal with double authorization. After parents (both treatment and control groups) provide online consent to participate in PW they will be contacted by the research team who will provide the parents with access information for the web-portal. The primary contact with the parents will be by telephone and subsequently through texts or web-portal notifications. Due to variation in study inclusion dates, parents enter the study on a rolling basis.

#### Parent-web (treatment) group

Following login to the portal, parents are asked to fill in the T1-survey. Parents in the Parent-web (treatment) group gain access to the PW following T1 data collection. As they complete sessions, parents are invited to a new session of PW. When finished they will be asked to fill in the new survey (T2) via the web-portal.

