### Measurement

Measurement will occur at three (i.e., T1, T2, T3) time periods (See Table 1 Schedule of enrollment, interventions, and assessments). First, pre-test measurement (T1) will occur directly prior to participants’ engagement in the internet-delivered parent training program but following their informed consent. Second, posttest measurements (T2) will be taken following completion of the internet-delivered training program at approximately 6 to 8-weeks following pre-measurement. T3 will only occur for the comparison condition parents who after the wait-list time period will have completed the Parent Web.

**Table 1 pone.0284926.t001:** Schedule of enrollment, interventions, and assessments.

			0	T1		T2		T3
Activity/assessment	Staff Member roll	Approximate time to complete	Pre-study consent, all groups	Pre-test Baseline, all groups	Parent Web, PW group 6–7 weeks	Post-test, all groups 6-8weeks	Parent Web, control group 12-15weeks	Follow-up, control group 12-16weeks
Consent			x					
Access to web-portal				x				
Demographics, background information				x				
COVID-parent				x				
SDQ				x		x		x
DBD-OD				x		x		x
FCU				x		x		x
PARCA				x		x		x
PSS				x		x		x
HAD				x		x		x
ASQ				x		x		x
Fidelity measures				x		x		x

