### Interventions

#### Internet-delivered parent training (Parent Web)

The Parent Web is an internet-delivered parent training program consisting of five main modules: an introductory and goal-setting module and four working modules targeting: 1) Increasing the time spent with your adolescent, 2) Listening to and validating your adolescent, 3) Choosing your battles and using problem solving techniques, and 4) Balancing your adolescent’s need for independence while still being responsible for her/his well-being. Additionally, there are six optional bonus modules about concerns parents might have (youth psychological ill-health, household responsibilities, school-related problems, friends and bullying, internet and Internet-based games, alcohol, and drugs). The delivery of the bonus sections is based on specific family need and preferences. The modules are ordered such that the priority is to facilitate a trusting and caring parent-adolescent relationship. In later modules, skills for improved handling of conflicts and adolescent independent behaviors are introduced. Each module encloses facts in written text, illustrations, movie clips with interviews, lectures, or role-played parent-adolescent conflict/modeled situations and includes exercises and homework expected to take about 1 hour to complete. Bonus sections are shorter and focus on information and strategies for handling specifically challenging situations. Each parent is assigned a “family guide” who communicates through the web-portal and provides reminders about working through the modules, short feedback on homework/exercises, and answers questions posed by parents weekly. Parents are required to be active by for example answering questions, reflecting on information/video-clips, and completing homework to access the next module. The program takes on average 6–7 weeks to complete depending on the time needed for each module and the number of bonus sections completed. The program is based on social learning- and developmental theory and the parenting skills provided are in line with those learned in cognitive behavior therapy parent training programs.

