#### Control group

Following login to the portal, parents are asked to fill in the T1-survey. Approximately 6–8 weeks later, when treatment group parents have completed their participation in PW, parents in the control group are invited to complete T2 data collection. Parents in the control group gain access to the PW following T2 data collection. When they are finished, they will be invited to a new survey (T3) via the web-portal.

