### Data analysis plan

The main hypothesis that participants in the Parent Web condition will exhibit intervention-related pre- to posttest benefits relative to participants in the comparison group will be evaluated using two-wave two-group latent curve models [42] for each of the outcome variables. The pretest level of each outcome will be modeled as a latent intercept, and pre- to posttest change in the outcome will be modeled as a latent slope. Group 1 will be the intervention group comprised of participants in Parent Web. Group 2 will be the matched wait-list control comparison group.

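### The post-test in the Parent Web group is triggered by finishing the programme, with no stated route for parents who do not finish, while controls are invited on elapsed time

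*Protocol article*

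**What the plan says.** All references are to the protocol article.

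- **Parent Web group, procedure** (Data collection and management plan, Parent-web (treatment) group): "When finished they will be asked to fill in the new survey (T2) via the web-portal".
- **General rule** (Measurement): "posttest measurements (T2) will be taken following completion of the internet-delivered training program at approximately 6 to 8-weeks following pre-measurement". This sentence carries both an event (completion) and a time window.
- **Schedule** (Table 1): "Post-test, all groups 6-8weeks".
- **Control group, procedure** (Control group): "Approximately 6–8 weeks later, when treatment group parents have completed their participation in PW, parents in the control group are invited". The Control section under Interventions likewise puts the end of the wait at 6 to 8 weeks.
- **What finishing requires** (Internet-delivered parent training): parents must be active, which includes "completing homework to access the next module". On duration: "The program takes on average 6–7 weeks to complete depending on the time needed for each module". The number of optional bonus sections also affects it.
- **Analysis group** (Data analysis plan): "Group 1 will be the intervention group comprised of participants in Parent Web".
- **Power** (Model estimation and model testing): 144 per group, a difference of .50 in latent slopes, loadings of .70, three indicators per wave, power .88.

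The article gives no expected completion rate. The Discussion treats completion as something the trial will help to establish.

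**The concern.** The main result is a comparison of T1-to-T2 change between two groups. In one group the instruction that produces T2 depends on what the parent does after baseline. In the other it does not depend on the parent's own behaviour. A Parent Web parent who stalls before the last module never meets the stated trigger, and the article gives no alternative.

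Three things are at stake. Post-tests may be missing for non-finishers in the Parent Web group only. The T1–T2 interval in that group follows each parent's pace, while the control interval does not. And the estimated change in the Parent Web group would rest on finishers, who may differ from non-finishers in motivation and family functioning. The groups are already non-randomised, so this would add a second source of selection, and an avoidable one. A T2 survey that was not sent in its window cannot be recovered in the analysis.

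**Working it through.** **1. The T2 rules side by side**

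| Source | Parent Web group | Control group |
|---|---|---|
| Group procedures | on finishing | about 6–8 weeks after T1, also linked to treatment-group completion |
| Measurement text | after completion, at about 6–8 weeks | not given separately |
| Table 1 | 6–8 weeks | 6–8 weeks |

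The sources agree for a parent who finishes inside the window. They diverge for a parent who stops, or who is still working when the window closes: Table 1 schedules a T2, and the group procedure has not yet triggered one. The control link to treatment-group completion cannot select control parents, because it does not depend on their own conduct. Entry is rolling, and no pairing of individual families for T2 timing is described.

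**2. The plan's own figure**

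The slope variance and pre–post correlation in the simulation are not given, so .88 cannot be reproduced uniquely. Assume two-sided alpha .05 and unit factor variance at both waves. Measurement error variance per wave on the factor scale is (1 − .70²)/(3 × .70²) = .51/1.47 = 0.347. The variance of observed change is 2(1 − r) + 2 × 0.347. With 144 per group and a difference of .50:

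- r = .5: variance 1.694, power .903
- r = .4: variance 1.894, power .869
- r = .3: variance 2.094, power .835

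The stated .88 lies within this range. It corresponds to a change-score SD of .50/[(1.960 + 1.175) × √(2/144)] = 1.353, which is used below.

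**3. Shift from observing finishers only**

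Let c be the share who finish and d the difference in mean change between finishers and non-finishers. Then the finishers' mean minus the mean of all treated families is (1 − c) × d. Both inputs are assumptions.

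- c = .8, d = 0.2: 0.04
- c = .6, d = 0.3: 0.12
- c = .5, d = 0.4: 0.20

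Against .50, reading that difference in latent SD, the range is 0.04/.50 = 8% to 0.20/.50 = 40%.

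**4. A second model: no programme effect**

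Let finishing be driven by a normal variable correlated ρ with change. The spurious difference is ρ × φ(z_c)/c × 1.353, where z_c is the standard normal quantile at c. The type I error is that of a two-sided 5% test of the slope difference. With ρ = .2 (assumed):

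| Completion | Spurious difference | Type I error |
|---|---|---|
| 90% | 0.053 | .062 |
| 80% | 0.095 | .087 |
| 70% | 0.134 | .119 |
| 60% | 0.174 | .157 |
| 50% | 0.216 | .198 |

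The sign follows that of ρ, which the article does not inform.

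**5. Power under the two T2 rules**

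All controls are taken as measured. The left column assumes that only finishers have T2 and that they show the full .50. The others assume that everyone is measured and non-finishers gain nothing.

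| Completion | Finishers only: power | Everyone: effect | Everyone: power |
|---|---|---|---|
| 90% | .86 | .45 | .81 |
| 80% | .84 | .40 | .71 |
| 70% | .81 | .35 | .59 |
| 60% | .78 | .30 | .47 |
| 50% | .73 | .25 | .35 |

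**The case against.** A reader might infer that non-completers have no post-test and that the trial reports a completers-only contrast. The article says neither. Table 1 and the Measurement text both give a 6–8 week window, and the average programme length fits inside it. The treatment-group paragraph can be read as the ordinary path through the portal and not as an exclusion. Group 1 is described as participants, not completers. Robust maximum likelihood could retain families with T1 only, under a missing-at-random assumption. Nor is the control invitation purely by calendar. These points stand, and they limit the finding to a risk created by the stated procedure.

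They do not remove it. The group paragraph is the only operational instruction for the Parent Web group, and it names finishing as the trigger. The article does not say that T1-only families will be retained. If they were, and T2 were missing for every non-finisher, the estimate would still rest wholly on finishing being unrelated to change given T1; d in the formula would then be whatever difference remains after T1 is accounted for.

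A reader might also infer bias towards benefit. That is plausible but not established: in a universal sample, parents with few concerns may be the ones who stop. Part of d could also be a real effect of receiving more of the programme, in which case the finishers' result answers a different question.

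Finally, analysis populations and missing-data methods are commonly left to an analysis plan, and their absence here is no fault. The T2 trigger is different: it is a data-collection rule that the article states, and states differently by group.

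**Conclusion.** The point holds as a risk of differential missingness. The stated T2 trigger in the Parent Web group depends on finishing, finishing depends on engagement, and no route is given for parents who stop or overrun. Controls face no such condition, and Table 1 shows a common window. The passages need reconciling.

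The size is illustrative only: a shift of 0.04–0.20 latent SD under assumed completion of 50–80% and an assumed difference of 0.2–0.4. It presumes that post-tests really are missing for non-finishers and that maximum likelihood recovers none of the difference. The direction is unknown. The loss of power from fewer T2 surveys is modest, about .81 at an assumed 70% completion. The larger cost is to interpretation: the estimate would lean towards finishers, whereas the Discussion looks ahead to offering the programme to parents in general.

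**What to change.** Reconcile the Measurement text and the treatment-group paragraph with Table 1. Every family with a T1 survey, in either group, should be invited to T2 at the same interval after T1, within the window already given, with the same reminders and regardless of modules completed. State that all these families belong to Group 1 or Group 2 in the main analysis. If the portal already works this way, one sentence confirming it is enough.

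The practical cost is small: a portal trigger and a few lines of text, for a survey that already exists. The statistical cost is not negligible. The estimate becomes the effect of offering the programme. If non-finishers gain nothing, an assumed 70% completion gives an effect of .35 and power near .59, against the planned .50 and .88. Some slower parents will be measured mid-programme; the planned monitoring of module coverage can show how many. Data collection began in Fall 2022, so the change cannot reach families whose T2 window has passed. For them, report how many Parent Web families have T1 but no T2, and the T1–T2 interval by group.

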#### Control group

Following login to the portal, parents are asked to fill in the T1-survey. Approximately 6–8 weeks later, when treatment group parents have completed their participation in PW, parents in the control group are invited to complete T2 data collection. Parents in the control group gain access to the PW following T2 data collection. When they are finished, they will be invited to a new survey (T3) via the web-portal.

### Data analysis plan

The main hypothesis that participants in the Parent Web condition will exhibit intervention-related pre- to posttest benefits relative to participants in the comparison group will be evaluated using two-wave two-group latent curve models [42] for each of the outcome variables. The pretest level of each outcome will be modeled as a latent intercept, and pre- to posttest change in the outcome will be modeled as a latent slope. Group 1 will be the intervention group comprised of participants in Parent Web. Group 2 will be the matched wait-list control comparison group.

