## Abstract

Well implemented, universal parental support is often effective in families with younger children, but research on their effects on families with adolescent children is scarce. In this study, a trial of the universal parent training intervention “Parent Web” in early adolescence is added to the social emotional learning intervention Promoting Alternative Thinking Strategies (PATHS®), completed in early childhood. The Parent Web is a universal online parenting intervention based on social learning theory. The intervention aims to promote positive parenting and family interaction through five weekly modules completed over 6–8 weeks. The main hypothesis is that participants in the intervention group will exhibit significant pre- to post- intervention-related benefits relative participants in the comparison group. The aims of this study are: 1) provide Parent Web as a booster aimed at improving parenting support and practices at the transition into adolescence to a cohort of parents whose children have previously participated in preschool PATHS, and 2) examine the effects of the universal edition of Parent Web. The study has a quasi-experimental design with pre- and post-testing. The incremental effects of this internet-delivered parent training intervention are tested in parents of early adolescents (11–13 years) who participated in PATHS when 4–5 years old compared to a matched sample of adolescents with no prior experience of PATHS. The primary outcomes are parent reported child behavior and family relationships. Secondary outcomes include self-reported parent health and stress. The proposed study is one of the few trials to test the effects of universal parental support in families of early adolescents and will therefore contribute to the understanding of how mental health in children and young people can be promoted across developmental periods through a continuum of universal measures.

**Trial registration:** Clinical trials.gov (NCT05172297), prospectively registered on December 29, 2021.

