### The Swedish PATHS® project

The Swedish PATHS trial was a cluster randomized trial conducted between April 2014 and June 2016 [2]. Briefly, the preschool edition of PATHS is a school-based, teacher implemented universal SEL intervention developed in the U.S. and designed to promote SEC in children as a foundation for improved mental health, academic success, and overall development [1]. PATHS is delivered as a curriculum by teachers and is developmentally focused on creating a caring and emotionally responsive school and classroom climate, and is grounded in theories about brain and social emotional development in children [1]. The PATHS trial assessed the short-term (pre- to posttest) effects of PATHS in an urban Swedish preschool setting. Participating children were four to five years old (N = 285; 140 PATHS intervention group; 145 wait-list control group) and were included into the cluster (k = 26 preschools; 13 interventions; 13 wait-list control) randomized trial in two waves. Over the academic school year, children that participated in PATHS evidenced improvements in working memory and prosocial play but also showed higher occurrence of teacher-rated hyperactive behaviors compared to children in the control group. Additionally, girls in the PATHS group showed improvements in emotional knowledge and reduced anxiety relative girls in the control group [2]. Other research has examined PATHS- related outcomes in the original trial in terms of outcome moderation by income level of neighborhoods in which preschools were located [12].

In the upcoming study, the participants are the parents of the PATHS cohort children and will be recruited to the immediate intervention condition of the PW trial, with the goal to examine the effects of a universal edition of PW. The wider motivation for the upcoming study is to increase our understanding of how universally provided SEL during early childhood can be coupled with universally provided parent training programs in early adolescence to support families with children and adolescents across important developmental and transitional periods (i.e., from early childhood through early adolescence).

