## Materials and methods

### Aim, design, and setting

The proposed study aims to develop our understanding of how mental health in children and young people can be promoted across developmental periods through a continuum of universal measures. This study will be carried out as a non-randomized controlled experiment (i.e., quasi-experiment) with a matched wait-list control condition and with dependent pre- and post-tests [29]. The study examines the incremental effects of an internet-delivered parent training for parents of early adolescents (11–13 years old) who participated in a preschool implemented social-emotional learning (SEL) intervention (PATHS) when 4–5 years old (i.e., intervention group) compared to a matched sample (i.e., comparison group).The main hypothesis is that participants in the intervention group will exhibit significant pre- to posttest intervention related benefits relative participants in the comparison group on several key outcomes.

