### Target population and sample size

The target population for this study is the parent(s) of the 144 children (now 11–13 years old) that participated in the Swedish PATHS project (i.e., immediate intervention group) along with the parent(s) of a matched sample of 144 children (i.e., comparison group) for a total sample size of 288 families. Inclusion criteria is that the child took part in the Swedish PATHS intervention trial and their parents consented to have future contact with the PATHS research group and that the child and participating parents presently live in Sweden.

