## Discussion

This study will offer understanding of how interventions can promote children’s mental health when delivered at different developmental stages. Findings will increase our understanding of the extent to which a SEL program delivered by teachers in preschool may have long lasting effects on adolescents’ mental health. Further, results will provide knowledge regarding the possible booster effects of an online parenting program (PW) on adolescents’ mental health. Considering the high numbers of children and adolescents with mental health problems and disorders [46, 47], especially during COVID-19 [48] it is of value to assess the usefulness of tools for mental health promotion as well as for prevention of problems during childhood and adolescence. Although universal, the intervention may be useful for parents and adolescents in need of further support and could reduce the use of mental health care resources. The universal aspect of the program could encourage positive family interactions, reducing conflicts in this stage of adolescent independence. If the study implies significant gains, the intervention could easily be offered to parents in general which is beneficial regarding scale-up [49].

The present project promises several new insights and innovations that are noteworthy. Scientific contributions within the area of social emotional learning (SEL) pertain to the six- to eight-year follow up of the PATHS intervention, which will be conducted in this project (i.e., pre-test data). PATHS is a SEL intervention that aims to directly support the development of emotion regulation, a key aspect of social emotional competence. Long term follow ups are rare, especially outside of the U.S., and only two prior studies have followed-up preschool SEL intervention for more than four years. In this project, the long-term impact of an intervention to support preschool children’s social emotional competence will be documented. Furthermore, the project advances our knowledge about developmental trajectories relevant to emotion regulation and mental health, which can inform wider SEL interventions.

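### Between T1 and T2 Parent Web use and PATHS history coincide, so the planned contrast can test Parent Web in PATHS families but not a PATHS-by-Parent-Web booster or an effect in parents without PATHS

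*Protocol article*

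**What the plan says.** Group membership follows PATHS history. The section on the Swedish PATHS project says that parents of the PATHS cohort "will be recruited to the immediate intervention condition of the PW trial". The Abstract says they are "compared to a matched sample of adolescents with no prior experience of PATHS". Under Aim, design, and setting: "This study will be carried out as a non-randomized controlled experiment (i.e., quasi-experiment) with a matched wait-list control condition".

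The Data analysis plan says the main hypothesis "will be evaluated using two-wave two-group latent curve models". Models A to D, under Model specification, use pretest and posttest only. A third wave is collected in one group: "T3 will only occur for the comparison condition parents who after the wait-list time period will have completed the Parent Web". Table 1 schedules all seven outcome scales at T3.

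The stated targets go further than a comparison of PW with a wait-list. The Introduction and the aim section speak of incremental effects. The Discussion says that "results will provide knowledge regarding the possible booster effects of an online parenting program (PW"), that the trial will examine PW at the universal level, and: "If the study implies significant gains, the intervention could easily be offered to parents in general".

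**The concern.** Every family that takes PW between T1 and T2 is a PATHS family, and every family that waits is described as PATHS-naive. One difference in change then carries three things: the effect of PW itself, any extra effect of PW because of earlier PATHS, and any difference in natural trend between the cohorts. A positive result could be reported as a booster effect, or as support for offering PW to parents at large, when the contrast contains no information specific to either. The limitations paragraph mentions reduced generalizability and the quasi-experimental design, but not this aliasing.

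**Working it through.** **The plan's own figure.** Inputs from Model estimation and model testing: 144 per group, slope difference .50, loadings .70, three indicators per wave, power .88. Not stated, and assumed here: two-sided alpha .05 and the latent variances.

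- Error variance per wave on the factor scale: .51 / (3 × .49) = .347.
- Slope variance 1: variance of change 1 + 2 × .347 = 1.694; power .903 in closed form, .898 by simulation (3,000 replications).
- Unit variance at each wave, correlation .5: .903 and .902. Correlation .4: .869 and .866.
- T2 loading held at exactly .70 with factor variance 2: .844 and .830.

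The stated .88 lies in this range. It implies a standard error of .50 / (1.960 + 1.175) = .50 / 3.135 = .159, or a change SD of 1.353.

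**What the contrast contains.** Let τ be the T1-T2 trend without PW in PATHS-naive families, τ′ their T2-T3 trend, θ the PW effect in PATHS-naive families, β the PATHS-by-PW synergy, and γ the PATHS-related difference in trend.

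- Intervention change T1-T2: τ + γ + θ + β
- Control change T1-T2: τ
- Control change T2-T3: τ′ + θ

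Planned contrast: D1 = θ + β + γ. These four settings all give D1 = .50:

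| θ | β | γ |
|---|---|---|
| .50 | 0 | 0 |
| .30 | .20 | 0 |
| 0 | .50 | 0 |
| 0 | 0 | .50 |

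The .88 is power for this sum. With baseline and PATHS level added there are 6 parameters, and the four T1-T2 cell means have rank 4. With γ = 0 the rank is 4 of 5, so θ and β still do not separate. Only their sum, PW in PATHS families, is then estimable.

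**What control T3 adds.**

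- D2 = control T2-T3 change minus control T1-T2 change = θ + (τ′ − τ). This equals θ if the trend is the same over both intervals.
- D3 = intervention T1-T2 change minus control T2-T3 change = β + γ + (τ − τ′). This equals β only if, in addition, γ = 0.

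Ranks with T3: 5 of 7 with τ′ free, 5 of 6 with τ′ = τ, and 5 of 5 with τ′ = τ and γ = 0.

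**Precision of D3.** It compares two independent groups. With 144 complete in each and the same change SD, its standard error is again .159.

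- Detectable at 80% power: 2.80 × .159 = .447, about .45.
- Power: .88 for .50, .35 for .25, .24 for .20.
- A synergy of .25 needs about 461 per group for 80% power.

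**Precision of D2.** It is a within-family second difference with variance 2 × 1.353² × (1 − r) / 144, where r is the correlation between a family's two successive changes. The documents do not give r, so a range is assumed.

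- r = 0: standard error √(3.66 / 144) = .159, detectable about .45.
- r = −.5 (equal correlation among the three waves): √(5.49 / 144) = .195, detectable 2.80 × .195 = about .55.

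**The case against.** The strongest reply is that the protocol never defines booster as an interaction. Aim 1 is to provide PW as a later intervention to PATHS families, and the main hypothesis claims only more pre-post benefit than the wait-list. On that reading, what PW adds for PATHS families is θ + β, which the planned contrast estimates under parallel trends. This stands. A reader might infer that the trial cannot answer its main question, and the documents do not support that. The reply does not cover the Discussion's booster findings if they are read as synergy, nor its remarks on universal effectiveness and parents in general.

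The limitations do say that prior PATHS participation weakens generalizability. That is partial disclosure, and it does not tell the reader that PW and PATHS history are inseparable at T2.

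An analysis of T3 may sit in a statistical analysis plan that is not shown. That is fair, so the absence of T3 from the article is not by itself the fault. The aliasing between T1 and T2 comes from the design, and no such plan could remove it.

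Two further readings are tempting. One is that the T3 data would separate PW from a booster. They do not on their own: there is no PATHS group without PW, and D3 still carries γ, along with time, repeat-testing and completer-selection effects. The other is that the sentence "Inclusion criteria is that the child took part in the Swedish PATHS intervention trial" shuts out every comparison family. The sentence before it defines the comparison group, so that reading is too literal. How the registry pool is cleared of earlier PATHS children is operational detail that an article may omit.

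**Conclusion.** The point holds as a mismatch between estimand and claim. The T1-T2 contrast is PW in PATHS families versus no PW in PATHS-naive families. If trends are parallel, it tests the main hypothesis. It gives no evidence on synergy and none on parents without PATHS, whatever its size or p-value.

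The scheduled T3 data can supply an estimate for PATHS-naive families if the trend is equal over both intervals. Table 1 makes these similar in length (T2 at 6-8 weeks, T3 at 12-16). The estimate remains open to repeat-testing effects and to selection, because T3 is described for controls who have completed PW. A synergy estimate needs the further assumption of no PATHS-related trend, which this design cannot test. Its precision suits only a synergy of about .45, nearly the whole planned effect of .50. The precision figures assume complete data and the change SD implied by the stated power.

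**What to change.** 1. Label the T1-T2 estimand as PW in PATHS families versus no PW in PATHS-naive families, and list the aliasing of PW with PATHS history as a limitation.
2. Prespecify a secondary three-wave analysis in the comparison group, with control T2-T3 change minus control T1-T2 change as the estimate of PW in PATHS-naive families. State the equal-trend assumption and the repeat-testing and completer-selection caveats. Base general-population statements on this estimate.
3. Treat intervention T1-T2 change minus control T2-T3 change as exploratory, with its assumptions and low power stated; otherwise drop the booster and synergy wording.
4. Separately, reconcile the 144 PATHS children under Target population and sample size with the 140 PATHS recipients (and 145 wait-list children) in the account of the earlier trial. State whether that trial's wait-list children can enter Group 1, since PATHS exposure would then vary within it.

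The cost is some added analysis, revised wording and a more modest claim. T3 is already scheduled, so no new measurement or contact is needed, which matters because data collection began in Fall 2022.
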